## Abstract

**Background:**

Adherence to adjuvant endocrine therapy is affected by medication side-effects and associated distress. Previous interventions focused on educating women to enhance adherence have proved minimally effective. We co-designed an Acceptance and Commitment Therapy (ACT) intervention to enhance medication decision-making and quality of life by targeting a broader range of factors, including side-effect management and psychological flexibility. This study aims to establish key trial parameters, assess the acceptability of the intervention and the extent to which it can be delivered with fidelity, and to demonstrate “proof of principle” regarding its efficacy on primary and process outcomes.

**Methods:**

The ACTION intervention includes an individual 1:1 ACT session followed by three group sessions involving 8–10 women and two practitioner psychologists. Participants are also provided with access to a website containing evidence-based methods for self-managing side-effects. The ACT sessions were adapted during the COVID-19 pandemic to be remotely delivered via video conferencing software. To evaluate the feasibility and acceptability of this intervention, a multi-site, exploratory, two-arm, individually randomised external pilot trial with a nested qualitative study will be undertaken. Eighty women with early stage breast cancer prescribed adjuvant endocrine therapy will be randomised (1:1) to receive treatment as usual or treatment as usual plus the ACTION intervention. The planned future primary outcome is medication adherence assessed by the ASK-12 measure. Progression to a phase III RCT will be based on criteria related to recruitment and follow-up rates, acceptability to patients, competency and fidelity of delivery, and proof of principle for change in medication adherence.

**Discussion:**

This external pilot trial will be used to ascertain the feasibility of undertaking a future phase III RCT to definitively evaluate an ACT-based intervention to support medication taking behaviour and quality of life in women with early stage breast cancer on adjuvant endocrine therapy.

**Trial registration:**

ISRCTN: 12027752. Registered 24 December 2020, 10.1186/ISRCTN12027752

## Background

Breast cancer is the most commonly diagnosed cancer in women worldwide [1]. In the UK, there are approximately 55,000 cases occurring per annum, with 11,000 cancer-related deaths [2]. Most breast cancers are oestrogen receptor positive (ER+) tumours. Treatment with adjuvant endocrine therapy (AET) such as Selective Oestrogen Receptor Modulators (SERMs, e.g. tamoxifen) and Aromatase Inhibitors (AIs e.g. letrozole, anastrozole, exemestane) for 5–10 years is standard care for women with ER+ tumours [3]. However, non-adherence is common with up to three-quarters of women prescribed adjuvant endocrine therapy (HT) taking < 80% of prescribed therapy and similar proportions discontinuing prematurely [4]. Low adherence and early cessation of AET are associated with an increased risk of breast cancer recurrence and all-cause mortality [5–12].

A broad range of behavioural and psychological variables such as mood, illness and treatment beliefs, and motivation are associated with adherence [13–15]. Medication side-effects are also frequently reported to affect adherence to HTs [4]. Common side-effects include hot flushes and night sweats, which affect up to 85% of women treated for breast cancer [16], and can compromise quality of life [17, 18]. Several other frequently reported medication side-effects may also affect adherence to HTs, including joint pain, vulvovaginal symptoms and sleep disturbance [19]. Most symptoms occur in the first year of using HT, suggesting this period could be the optimal opportunity for delivering supportive care for this patient group [20–22].

Adherence interventions evaluated so far have largely been ineffective [23–25]. A meta-analysis of 8 such interventions yielded a small to moderate heterogenous effect in favour of the interventions [24]. The interventions largely focussed on educating patients regarding AET and did not consistently address the range psychological factors that contribute to non-adherence. Broadening the focus to target emotions and self-management of side-effects could support adherence and quality of life in women who struggle with adhering to hormone therapy.

Acceptance and Commitment therapy (ACT) is a type of cognitive behaviour therapy that uses techniques such as mindfulness, goal setting, and perspective taking to engender psychological flexibility: “ … the capacity to persist or to change behaviour in a way that includes conscious and open contact with thoughts and feelings, appreciates what the situation affords, and serves one’s goals and values” [26]. ACT may be a suitable approach in this setting for two main reasons [13, 27–30]. First, psychological flexibility is a broad treatment target comprising a range of emotional and motivational factors that may contribute to non-adherence. Second, ACT is suitable to helping people with health conditions, largely because it does not focus on changing understandable emotional responses to illness (e.g. frustration, anxiety etc.). Instead, ACT encourages finding ways to live well alongside these difficult experiences to enable engagement in meaningful everyday activities [28, 31].

We propose that ACT could be used to support functioning and medication adherence with women who have experienced a life-threatening event such as breast cancer, and are being asked to return to everyday life while managing treatment-related challenges. There is a growing evidence base supporting ACT as a means to improve functioning, quality of life, and mood in chronic disease and pain [28, 32]. Although all have methodological limitations, several ACT trials with cancer populations have noted post-intervention improvements in outcomes, such as psychological distress and quality of life [28, 33–36]. There are no definitive trials of ACT for improving adherence to medication, with evidence limited to case series among people with diabetes and HIV [29, 37, 38].

We co-designed an intervention based on ACT principles through extensive engagement with patients and healthcare professionals [39]. The aim was to co-design an intervention that was acceptable to patients and implementable within the United Kingdom (UK) National Health Service (NHS). In patient focus groups we explored women’s experience of AET, perceptions regarding the acceptability of ACT, and preferences for intervention format. Healthcare professional interviews explored the acceptability and feasibility of an ACT intervention delivered within the NHS. In a co-design workshop, attended by patients and healthcare providers, we co-designed the configuration of the intervention. This process occurred prior to the coronavirus disease 19 (COVID-19) pandemic. We altered the co-designed intervention so that it could be delivered via video-conferencing software instead of in person. The aim of the adaption was to ensure the ACTION intervention could be delivered in the context of potential future changes in how clinical psychology services will provide psychological interventions, and to ensure it could be delivered while social distancing guidelines were in place for a clinically vulnerable population.

The aim of the ACTION trial is to test the feasibility of undertaking a definitive phase III parallel groups randomised controlled trial (RCT) of an ACT-based intervention for improving adherence to hormone therapy in women following curative treatment for breast cancer.

The objectives are to:i)Establish eligibility, recruitment, retention and follow-up rates to inform the design of a phase III RCT;ii)Assess the acceptability of the intervention and protocol to participants and NHS therapists;iii)Assess the extent to which NHS therapists can remotely deliver an ACT intervention with fidelity, following remotely delivered training;iv)Demonstrate “proof-of-principle”, via exploration of between-group change in outcomes (medication adherence, quality of life, mood) and process (psychological flexibility) variables.

## Methods

### Design

This is a multi-site, exploratory, two-arm, individually randomised pilot RCT with a nested qualitative study. Eighty women with early stage breast cancer will be randomised (1:1) to receive treatment as usual or treatment as usual plus the ACTION intervention. The study has been approved by the York and South Yorkshire Health Research Authority Research Ethics Committee (20/YH/0104), and is a registered clinical trial (ISRCTN12027752). The study is presented according to recommendations of the SPIRIT [40] and CONSORT extension for pilot and feasibility trials [41] (Appendix 1). The intervention being evaluated is described using the TIDieR checklist [42] (Appendix 1).

### Setting

We will identify and recruit participants from oncology services at NHS hospitals in Yorkshire, UK. Sites with existing or planned implementation of a psychological intervention designed to improve adherence to HTs will be excluded. A single site will be responsible for delivering the intervention (Leeds Teaching Hospitals NHS Trust). Eligibility criteria for the delivery site include access to a Health and Care Professional Council (HCPC) registered practitioner psychologist (Clinical, Health or Counselling Psychologist) to deliver the intervention alongside at least one additional supporting member of staff (e.g. psychologist in training, assistant psychologist, counsellor, nurse therapist, or other HCPC registered staff). The delivery site must also have access to video conferencing software with the ability to create virtual breakout rooms, which can accommodate groups of 8–10 individuals.

### Participants

Women aged over 18 and using tamoxifen, raloxifene, anastrozole, letrozole, or exemestane as part of their adjuvant endocrine therapy for early stage (1 to 3a) breast cancer are eligible. Full eligibility criteria are shown in Table 1.

**Table 1 Tab1:** Eligibility criteria for participation in the ACTION trial

1. Written (signed and dated) informed consent 2. Capacity to provide informed consent 3. Women with early stage (1 to 3a) breast cancer according to the TNM/American Joint Committee on Cancer (AJCC) staging system 4. Aged ≥ 18 years at time of screening for ACTION 5. Have sufficient proficiency in English to contribute to the therapy sessions and data collection required 6. Treated with curative intent 7. Completed their hospital-based treatment (e.g. surgery, radiotherapy and/or chemotherapy). Women are still eligible for the study before completing Herceptin. 8. Currently prescribed oral adjuvant Hormone Therapy (tamoxifen, raloxifene, anastrozole, letrozole, exemestane) 9. The participant is willing to be audio recorded during the therapy sessions 10. The participant is willing to complete the study questionnaires 11. The participant is willing and able to attend all intervention sessions and/or complete therapy workbook 12. The participant is willing and able to access all sessions remotely via video call	1. Stopped taking adjuvant hormone therapy if it is clinically contraindicated according to clinical recommendation 2. Currently or recently (last 6 months) involved in another psychotherapy (e.g. using CBT/ACT, mindfulness) research study where medication adherence is a primary outcome 3. Those who are unable to access the sessions remotely via a video call 4. Currently attending, or on a waiting list for psychotherapy/psycho-oncology/psychology/counselling services, for any reason (related to medication or not) 5. Current diagnosis of an active major mental health disorder likely to interfere with participation (e.g. active psychosis, significant issues with addiction or self-harm) 6. Known element of risk (e.g. clinical team are aware that patient has made a recent attempt to end their life, or has recently disclosed plans to do so) as determined by three clinical screening questions below, (i) Recently (in the last month), have you had any thoughts about ending your life? * (ii) Have you thought about how you might go about it? (iii) Do you intend to carry out this plan? * a patient is only excluded if they answer ‘yes’ to question 6 (iii)

### Study processes

Participant identification can be via three routes (Fig. 1):

**Fig. 1 Fig1:**
[figure not shown]
CONSORT diagram illustrating participant flow through the ACTION trial

1) A research nurse (or delegate) will screen patient records for eligible patients attending their final hospital appointment following completion of their hospital-based treatment;

2) An oncologist will screen patients discharged following treatment who self-refer to discuss problematic medication side effects and/or adherence problems;

3) A research nurse (or delegate) will retrospectively screen patient records for potentially eligible patients who have completed treatment within the last 6 months.

Sites will complete a screening form for all patients who have completed their hospital-based treatment for early stage breast cancer. The screening form will capture age, staging, ethnicity, and whether or not a patient is randomised. Screened patients who are not randomised will have the reason they are not eligible or declined participation recorded. Screening forms will not contain identifiable information.

For recruitment routes 1 and 2, a member of the patients care team will introduce a research nurse (or delegate) to the patient. For recruitment route 3, the research nurse or delegate will contact the patient by post. For all routes, a study invitation pack will be provided containing a participant information sheet, contact details, consent form, and a baseline questionnaire. Patients will have the opportunity to consent after considering the opportunity and asking questions, and may consent immediately once they are screened and confirmed as eligible. A research nurse will confirm eligibility among interested women, record consent, and ask the participant to complete the baseline questionnaire. Eligibility and consent discussions, and completion of baseline measures may take place in person at the hospital site or remotely. The site Principal Investigator (or delegate) is responsible for the informed consent of participants at their site.

Following informed consent, confirmation of eligibility and receipt of the baseline questionnaire, participants will be randomised by the research site using the University of Leeds Clinical Trials Research Unit (CTRU) randomisation system. Participants will be randomised on a 1:1 basis to receive either treatment as usual or treatment as usual plus the ACTION intervention and will be allocated a trial number. A computer-generated minimisation programme that incorporates a random element will be used to ensure treatment groups are well-balanced for the following stratification factors: recruiting site, recruitment route (recently completed treatment vs. experiencing medication problems vs. retrospective screening), participant age (≤ 50 years vs. > 50 years and < 70 years vs. ≥ 70 years).

Participants, therapists, research nurses/delegates at site, participant’s GP and staff at the Clinical Trials Research Unit (CTRU) will be not be blinded to the randomised allocation. Following randomisation the research nurse will notify the participant of their allocation, and the therapists will be informed about participants allocated to the intervention arm.

All participants will be requested to complete a follow-up questionnaire at 3 months post-randomisation. Participants recruited at least 3 months prior to the end of the recruitment period will also be invited to complete a questionnaire at 6 months post-randomisation. Participants will have the option to receive questionnaires by post or online. Non-responders will be reminded using postal, telephone, online and text prompts.

A clinician may decide that a participant should be withdrawn from the intervention if there is reason to believe they have become unsuitable for the study. Participants can also withdraw from one or more of the following: intervention, data collected from them via questionnaires or data about them from medical records.

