### Sample size

As the study is randomised and we wish to obtain a preliminary estimate of effectiveness in relation to demonstrating how the intervention affects medication adherence, we have used methods developed for phase II screening trials in oncology [59] in which preliminary and non-definitive randomised treatment comparisons are made, carefully adjusting the false-positive (a) and false-negative (ß) error rates so the target treatment effect is appropriate while the sample size remains restricted. Allowing for 25% loss to follow-up and using a 1-sided *t* test with a significance level of 20% will allow us to detect an effect size of 0.432 with 65% power using a sample of 80 patients. The sample size must be sufficient to establish consent and dropout rates (Objective i) and test trial protocols and acceptability (Objectives ii–iii). A sample size of *N* = 40 per arm will be sufficient to meet these aims [60–62].

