### Analysis

A detailed statistical analysis plan will be written before any analysis is undertaken. The analysis will focus on descriptive statistics and confidence interval estimation rather than formal hypothesis testing and no formal evaluation of safety or efficacy of the study interventions will be conducted. All analyses will be undertaken on the intention-to-treat population, with all participants included in the analysis according to their randomised allocation, and regardless of non-adherence to the intervention or withdrawal from the study. Final analysis will be conducted once all available outcome data is received.

Descriptive summaries will be presented overall, by arm and by site (where relevant) using appropriate frequencies and summary statistics. Outcome measures will be scored according to relevant scoring manuals. To generate evidence of proof of principle, the mean change from baseline in the three and 6-month ASK-12 scores in both arms will be reported, together with a range of confidence intervals around the main estimate to inform us as to the likelihood of where the ‘true’ estimate may lie. Analysis will adjust for the minimisation factors.

The trial is not powered to provide a precise estimate of the level of clustering relating to therapist effects, but we may be able to investigate this effect. If a sufficient number of therapists are involved in delivering the intervention, we will estimate the intraclass correlation coefficient and produce a range of confidence intervals (e.g. 95%, 67% and 51%) around this to inform the sample size of the definitive trial.

The semi-structured interviews will be analysed using thematic analysis [63].

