### Study status

#### Enrolling

Recruitment began 04/2021. Approximate date recruitment will be completed: 09/2022. Latest protocol version approved 5.0_030221 on 05/02/2021 by Yorkshire & The Humber–South Yorkshire Research Ethics Committee (20/YH/0104).

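### The sample-size section gives one analysable number (60) with no time point, but late recruits are never sent the 6-month questionnaire and the 25% loss allowance does not cover them

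*Protocol article*

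**What the plan says.** The Sample size section gives one calculation. "Allowing for 25% loss to follow-up" and taking a one-sided t test at the 20% level, it says the design "will allow us to detect an effect size of 0.432 with 65% power using a sample of 80 patients". Eighty less 25% is 60 analysable women, 30 per arm. No time point is attached to the calculation.

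The Analysis section rests proof of principle on ASK-12 at two times: "the mean change from baseline in the three and 6-month ASK-12 scores in both arms will be reported", with a range of confidence intervals.

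Under Study processes, every participant is asked for a 3-month questionnaire, but only those enrolled at least 3 months before recruitment closes "will also be invited to complete a questionnaire at 6 months post-randomisation". Table 3 repeats the restriction in its 6-month column.

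Study status gives the recruitment window: "Recruitment began 04/2021. Approximate date recruitment will be completed: 09/2022".

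**The concern.** A woman who is never invited at 6 months is missing by design. She is not a dropout, and the sample-size statement makes no mention of her. A reader who takes the 60 analysable women to apply at both times will expect more 6-month data than the design can deliver at the stated loss rate.

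The 6-month score matters here. The intervention section allows the individual session to take place up to 3 months after randomisation and the first group session up to six weeks after that. Appendix 1 spaces the three group sessions two weeks apart. The last session can therefore fall about 10 weeks after month 3, or about 5.3 months after randomisation. A woman treated late within these limits may give her 3-month score before any therapy, and only her 6-month score follows the whole programme. Table 3 also collects the two acceptability measures at 6 months only, and one of them feeds the progression criteria.

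At stake is how the 6-month signal is read: fewer women and wider intervals than the sample-size section suggests.

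**Working it through.** **Inputs.** From Sample size: 80 randomised, 25% loss, one-sided 20%, standardised effect 0.432, power 65%. From Design: 1:1 allocation. From Study processes: the 3-month cut-off for the 6-month invitation. From Study status: recruitment from April 2021 to about September 2022, so T = 17 to 18 months. Assumed, because the document gives neither: even accrual, and the 25% applying to invited women.

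**Step 1. The plan's own figure.** n = 80 × 0.75 / 2 = 30 per arm. Power = 1 − F(t_crit), where F is the noncentral t distribution with 2n − 2 degrees of freedom and noncentrality d√(n/2), and t_crit is the one-sided critical value. The noncentrality is 0.432 × √15 = 1.673.

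- One-sided 20%, as written: normal approximation Φ(1.673 − 0.842) = 79.7%; noncentral t 79.6%. The stated 65% is not reproduced.
- One-sided 10% (equivalently two-sided 20%): normal Φ(1.673 − 1.282) = 65.2%; noncentral t 64.8%. The stated 65% is reproduced.

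The stated level and the stated power therefore do not fit together at 30 per arm, whatever the time point. Both levels are carried forward.

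**Step 2. Number invited at 6 months.** The late-recruit share is f = 3/T, which is 3/18 = 16.7% to 3/17 = 17.6%. Invited: 80 × (1 − f) = 66.7 to 65.9.

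**Step 3. Number analysable at 6 months.** N = 80 × (1 − f) × (1 − loss). With 25% loss, N = 50.0 to 49.4, about 25 per arm. The missing share is 37.5% to 38.2%.

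**Step 4. Sensitivity to the two assumptions.**

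| Late recruits | Loss among invited | Analysable | Missing |
|---|---|---|---|
| 5% | 25% | 57 | 29% |
| 16.7% to 17.6% | 25% | 50 to 49 | 38% |
| 25% | 25% | 45 | 44% |
| 16.7% to 17.6% | 10% | 60 to 59 | 25% to 26% |

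The last row shows when the 25% allowance would cover 6 months as well: loss among invited women would have to be about 10%.

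**Step 5. Power and detectable effect (noncentral t).** At 25 per arm the noncentrality is 0.432 × √12.5 = 1.527.

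| Level | Power for 0.432, 30 per arm | Power for 0.432, 25 per arm | Effect detectable with 65% power, 30 per arm | Same, 25 per arm |
|---|---|---|---|---|
| One-sided 20% | 80% | 75% | 0.32 | 0.35 |
| One-sided 10% | 65% | 59% | 0.43 | 0.48 |

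**Step 6. Precision.** Interval width scales with 1/√N. √(60/50) = 1.095, so 6-month intervals are about 10% wider than 60 analysable women would give.

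**The case against.** The strongest reply is that nothing is contradicted. The sample-size statement claims nothing about 6 months. Everyone is followed at 3 months, so a 3-month reading is natural. The restricted 6-month follow-up is disclosed openly, and the article condenses a fuller protocol that may name the time point. This stands in part: the article never says that 65% power applies at 6 months. But it sets out one sample-size figure beside two ASK-12 time points, and the figure's analysable number can hold at 6 months only if loss among invited women is well below the stated 25%.

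A reader might go further and infer that the stated power fails at 6 months. The document's own test does not support that. At one-sided 20%, 25 per arm still gives 75%, above 65%. Even with 40% late recruits and 25% loss (36 analysed), power is 67%. The drop to 59% appears only at one-sided 10%, a level the document does not state, although it is the one that reproduces its 65%.

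It is also fair to say that the consequence is modest. The Analysis section plans estimation rather than formal testing, and the reported 6-month intervals will show their own width.

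**Conclusion.** The concern holds as a mismatch between the sample-size statement and the follow-up design. The 25% allowance does not account for women who are never invited at 6 months, and the time point for the 60 analysable is not named. Under even accrual over 17 to 18 months and 25% loss among those invited, about 50 women are analysable at 6 months. The cost is about 5 to 6 percentage points of power for 0.432, depending on the level used, and intervals about 10% wider.

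The 38% missing should not be read as a fixed consequence of the design. It depends on both assumptions and ranges from about 29% to 44% for late-recruit shares of 5% to 25% at 25% loss. It is about 25% if loss among invited women is only about 10%.

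A reader might also want the figure reduced further because one arm is treated in groups. The document gives no intraclass correlation from which to do this. It says the trial is not powered to estimate therapist clustering precisely, and it plans an estimate only if enough therapists take part. No clustering figure is therefore put forward here.

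**What to change.** In the Sample size section:

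1. Reconcile the significance level with the power. With 30 per arm and 0.432, one-sided 20% gives about 80% and one-sided 10% gives about 65%. The sponsor should check which calculation was run and correct the level or the power. Labelling the present sentence as the 3-month figure without this step would keep a number that its own inputs do not give.
2. State that 60 analysable women refers to the 3-month score.
3. Add the expected 6-month number (about 66 to 67 invited and about 50 analysable), with its accrual and loss assumptions and a short range.
4. Give the recalculated 6-month power (75% or 59%), or the effect detectable with 65% power (0.35 at one-sided 20%, 0.48 at one-sided 10%), to match the level settled in item 1.

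If an allowance for group delivery is added, label it as an illustrative sensitivity range.

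The cost is a few sentences. Enrolment does not change. The downside is a less favourable 6-month figure in print.
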